## **9.2 Qualitative evaluation**

Study 3: Qualitative data will be collected through telehealth-conducted interviews using a semi-structured interview guide formulated by the researchers and consumer collaborators to explore referrer, physiotherapy and participant experiences of the intervention. Interviews will be audio-recorded, transcribed and analysed using a Grounded Theory framework. The qualitative study will be reported separate to the main trial (Study 3 in figure above) and will have its own ethics application and consent procedures.

## **9.3 Cost effectiveness analysis**

We will also follow-up all participants at 52-weeks. We will ask them to complete all measures. This additional assessment will test any maintenance in treatment effect, and a cost effectiveness analysis if clinical effectiveness is demonstrated.

## 10. PARTICIPANT SAFETY

### 10.1 Risk Management and Safety

We anticipate no substantial risks nor safety concerns associated with participation in this study. Intervention group participants will be required to use the femfit® biofeedback device during their tele-health consultations and during their prescribed PFM HEP. The femfit® is a low-risk (class I) device which has undergone extensive electro-magnetic compatibility, biocompatibility and electrical safety testing and has been approved by the TGA[53]. Information regarding the use of an intra-vaginal biofeedback device will be included in all recruitment processes (study discussions with the research team member, information within the study). This will ensure women are aware that if randomised to the intervention group they will be asked to use this device and are therefore able to provide informed consent. Women randomised into the intervention group will receive detailed instructions (written in their study manual and verbal from the physiotherapist during their tele-health consultations) about how to insert and remove the femfit® sensor. As the femfit® sensor is smaller than an index finger, it is not anticipated that insertion of the sensor into the vagina would cause any discomfort to the woman. However, if an intervention group participant, during their involvement in the trial, experiences discomfort or distress using the femfit® device they will be asked to discuss this with their treating study physiotherapist and use of the femfit® may be discontinued.

We recognise that for some women receiving an invitation to participate in this study or completing the questionnaires may cause distress. If a woman experiences distress as a result of the invitation to participate or actual participation in the study, they will be directed to contact the Chief Investigator (A/[name]), in the PICF and participant study manual. The Chief Investigator will discuss with the woman the nature and severity of the distress and will determine what further action is required. Further action may include a request to contact their General Practitioner as soon as possible, withdrawal from part or all of the study intervention or withdrawal from the study. If deemed necessary additional action may also include:

- Review in the gynae-oncology clinic with a consultant gynae-oncologist
- Referral to psychology/psychiatry services at the referring health service, or in the local community, as appropriate
- Linking the woman with the health service consumer advocate
- Acute mental health assessment by the CAT team.

## 11. ADVERSE EVENT REPORTING

Due to the nature of the intervention, any risks to participants are likely to be minor and transient. The reporting and handling of all adverse events (AE) will be in accordance with NHMRC guidelines[55], which defines an AE as: “Any untoward medical occurrence in a patient or clinical trial participant administered a medicinal product and that does not necessarily have a causal relationship with this treatment” and a serious AE as any AE that: results in death; is life threatening; requires inpatient hospitalisation or prolongation of existing hospitalisation; results in persistent or significant disability/incapacity; is a congenital anomaly/birth defect. Due to the low-risk nature of the interventions in this trial, serious AE are extremely unlikely but will be reported to the primary Human Research Ethics Committee should they occur. We will record all adverse events, including minor, expected or unexpected (as described in the PICF), according to the NCI-CTCAE(v5) criteria [57]:

- Grade 1 Mild; asymptomatic or mild symptoms; clinical or diagnostic observations only; intervention not indicated.
- Grade 2 Moderate; minimal, local or non-invasive intervention indicated; limiting age-appropriate instrumental activities of daily living
- Grade 3 Severe or medically significant but not immediately life-threatening; hospitalization or prolongation of hospitalization indicated; disabling; limiting self-care activities of daily living

- Grade 4 Life-threatening consequences; urgent intervention indicate
- Grade 5 Death related to AE

Information regarding AE may be reported by participants in the 17 and 52-week follow-up assessment questionnaires in section E: Health problems. Adverse events may also be reported by the woman directly to the treating study physiotherapist or to a member of the research team. Any AE reported to the study physiotherapist will be recorded in the consultation notes and if serious will be reported to the research team to follow-up and action. Any AE reported to the research team will be either i) recorded in a custom-built 'Adverse Events Form' and then entered into a "Participant Adverse Event" excel spreadsheet or ii) entered directly into the excel spreadsheet (see 'Standard Operating Procedure: Adverse Event Reporting' document). This process will include the member of the research team ascertaining and subsequently recording the likelihood that the reported AE is related to the intervention. This will be done according to the NCI Guidelines for Investigators [58]:

| Relationship                                    | Attribution | Description                                       |
|-------------------------------------------------|-------------|---------------------------------------------------|
| Unrelated to investigational agent/intervention | Unrelated   | The AE is clearly NOT related to the intervention |
|                                                 | Unlikely    | The AE is doubtfully related to the intervention  |
| Related to investigational agent/intervention   | Possible    | The AE may be related to the intervention         |
|                                                 | Probably    | The AE is likely related to the intervention      |
|                                                 | Definite    | The AE is clearly related to the intervention     |

All AE will be reported to the internal Trial Advisory and Safety Committee who will be responsible for deciding what action if any is needed on a case-by-case basis.

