| Adverse Events                                | Adverse events (AE) will be defined as any change from the participant's baseline (pre-treatment) condition, other than improvement. Information about AEs will be collected in two ways:
i) self-reported within the follow-up questionnaires via a custom-developed table and/or
ii) reported directly to the research team as per section 7. 'Adverse event reporting' within this protocol.
All AE data will be aggregated. | Type of adverse events and proportions of participants experiencing each adverse event will be reported. | 17 and 52 weeks        |

| Health Economic Data                               | Description                                                                                                                                                                                                                                                                                                                                                                                            | Data                                                      | Time-points measured               |
|----------------------------------------------------|--------------------------------------------------------------------------------------------------------------------------------------------------------------------------------------------------------------------------------------------------------------------------------------------------------------------------------------------------------------------------------------------------------|-----------------------------------------------------------|------------------------------------|
| Cost of physiotherapist's time                     | The cost of physiotherapy services provided to each participant will be calculated by the research team.                                                                                                                                                                                                                                                                                               | Reported as the dollar cost per participant (mean and SD) | 17 weeks (Intervention group only) |

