#### *Study physiotherapists*

We will recruit 3 physiotherapists from our study sites and/or the broader community to deliver the tele-health consultations for both the pilot study and the RCT. Physiotherapists will be eligible if they i) have postgraduate training in pelvic floor physiotherapy; ii) are able to commit to accepting at least one new study participant for their per-protocol intervention each week; iii) agree to comply with all study processes and procedures. Advertisements will be circulated through our study sites and community-based women's health physiotherapy clinics. Eligibility will be assessed via response to a University of Melbourne Position Description. Physiotherapist will be paid for their involvement in

this pilot study/preliminary research. These physiotherapists will have participated in our pilot study (see 9.1.1).

Physiotherapists in the RCT will treat approximately 12 patients each. Study physiotherapists will receive a detailed study manual and will complete training in study processes and procedures (Refer to Table 1). Within the study manual, a 'consultation notes' template will be included and used to document each participant consultation. Physiotherapists can choose to complete consultation notes electronically or on paper, depending on their preference. Consultation notes will be returned to the research team, by the physiotherapist, at the completion of each participant's course of tele-health consultations.

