| 2. Instructor qualifications  | 
Professional qualification: physiotherapist with postgraduate training in pelvic floor physiotherapy.
 
Per-protocol study training: detailed study manual and training in study processes and procedures including:
 
 
- pelvic floor muscle assessment and exercise instruction processes;
 
- instructions for teaching use of the biofeedback device;
 
- biofeedback data export;
 
- practice video-consultations to practice video-consultation skills.
 
 
During the study: regular meetings with the research team to review per-protocol procedures and discuss/address potential issues as they arise.
 |
| 3. Individual or group        | Individual physiotherapist supervised telehealth-delivered instruction in PFMT and individual home-based PFMT.                                                                                                                                                                                                                                                                                                                                                                                                                                                                                                                                                                                        |
| 4. Supervision                | Supervision will be provided remotely by a trained physiotherapist via 8 telehealth-delivered consultations, over 16 weeks. Between tele-health consultations woman will complete their PFMT unsupervised.                                                                                                                                                                                                                                                                                                                                                                                                                                                                                            |

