| 16. Intervention fidelity                                       | 
Consultation notes will be reviewed and analysed by the research team to assess the physiotherapists’ adherence to trial protocols.
 
The research team will also conduct random audits of audio recorded consultations.
 
Both the consultation notes template and the specific criteria that will be applied to the consultation notes to evaluate fidelity will be developed in preliminary research (Pilot study) in consultation with the recruited physiotherapists.
                                                                                                                                                                                                                                                                                                                    |

\* Preliminary research: A pilot study will be conducted including consultation and co-design of resources and intervention processes and procedures with the recruited study physiotherapists (n=3) and women who have had gynaecological cancer treatment (n=3). All study materials will be created specifically for this intervention.

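### Section 11 promises to log all adverse events and report them to a committee, but forwards those told to the physiotherapist only when serious

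*Protocol*

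**What the plan says.** Section 11 makes two commitments without a seriousness threshold. The first is "We will record all adverse events, including minor, expected or unexpected", using CTCAE version 5 grades. The second is "All AE will be reported to the internal Trial Advisory and Safety Committee who will be responsible for deciding what action if any is needed".

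Between them stands the rule for the physiotherapist: "Any AE reported to the study physiotherapist will be recorded in the consultation notes and if serious will be reported to the research team". The next sentence covers the AE form, the spreadsheet and the judgement of relatedness, and applies to AEs reported to the research team.

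Other sections bear on the same route:

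- Section 8.2, Study physiotherapists: "Consultation notes will be returned to the research team, by the physiotherapist, at the completion of each" participant's course.
- Section 8.2, Table 1, item 16: "Consultation notes will be reviewed and analysed by the research team to assess" physiotherapists' adherence to trial protocols. No other purpose is given.
- Section 4.6, Adverse Events row: "Information about AEs will be collected in two ways", namely the follow-up questionnaires and reports made directly to the research team. For the latter it points to section 7.
- Section 10.1: if a woman has discomfort or distress with the device, "they will be asked to discuss this with their treating study physiotherapist".

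**The concern.** The seriousness condition works against both commitments around it. Section 11 expects risks to be minor and transient and serious events to be extremely unlikely, so forwarding only serious events leaves out nearly everything that the protocol expects to see. The condition is also not confined to the mildest grade. Under section 11's own definitions, a Grade 2 event that needs local treatment is not serious unless it also meets one of the listed serious criteria.

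The physiotherapist is also the person to whom section 10.1 sends device complaints. At stake is whether the AE log, and the committee that decides on action case by case, receive what the protocol says they will.

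**Working it through.** The plan gives no figure to reproduce, and the point does not depend on sample size, power or effect size. The check is to follow one event, non-serious and told only to the physiotherapist, through each written route.

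1. **Physiotherapist to research team (section 11).** The event is written in the consultation notes. It is not serious, so the forwarding rule does not apply.
2. **AE form, spreadsheet and attribution (section 11).** These start from an AE reported to the research team. Step 1 produced no such report.
3. **Consultation notes (section 8.2 and Table 1, item 16).** The notes reach the team when the course is complete. Their stated review is for fidelity. No sentence tells anyone to move an AE from them into the log.
4. **AE sources (section 4.6).** Two are listed, and the notes are neither of them.
5. **Monitoring (section 1.4).** The fortnightly meeting looks at AEs that have been reported. This one has not.
6. **Physiotherapist meetings (Table 1, item 2).** These are "regular meetings with the research team to review per-protocol procedures and discuss/address potential issues as they arise". AEs are not named and forwarding is not required, so passing the event on is possible but informal.
7. **The woman herself (sections 4.6, 10.1 and 11).** She can enter it in the 17- or 52-week questionnaire or tell the research team directly. If taking part distresses her, she is directed to the Chief Investigator. Each of these depends on her repeating what she has already told her physiotherapist.

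No written rule carries the event to the log or the committee during treatment unless the woman repeats it.

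**Delay.** The programme runs 16 weeks. Assume that the last consultation falls at week 16 and that the notes are returned at once. An event told at a consultation in week w then waits 16 − w weeks: 16 − 0 = 16 weeks from a first consultation at the start, and 16 − 16 = 0 weeks from the last. Up to 16 / 2 = 8 fortnightly meetings fall within the longest wait. This limits the delay before the notes arrive. It does not count events.

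**Two labels that do not match.** Section 7, cited in the AE row of section 4.6, is Data Collection; AE reporting is section 11. The committee named in section 11 has neither the name used in section 1.4 (meets fortnightly) nor the one in section 1.5 (meets twice a year).

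**The case against.** The strongest reply is that the rule concerns escalation. The quoted sentence goes on to say that serious events go to the team for follow-up and action. On that reading everything is written down, serious events are also raised promptly, and all notes later reach the team, where the commitment on all AEs takes over. This is a fair reading. It reduces the defect to a missing extraction step and a delay, but does not remove it: nobody is told to extract, and section 4.6 leaves the notes out.

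Unseen documents may also close the gap. The AE operating procedure, the study manual and the notes template are not shown, and any of them could carry an AE field or instruction. That stands as a limit on this point. However, the protocol cites the procedure for AEs already reported to the team, and a procedure that forwarded every AE would go beyond the protocol's own sentence.

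A reader might infer three stronger things that the documents do not support:

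- **That minor AEs are lost altogether.** They are written down, the notes reach the team, and both arms can report at 17 and 52 weeks.
- **That women are exposed to real danger.** Section 10.1 describes a low-risk device, does not anticipate discomfort from insertion, and allows device use to be discontinued.
- **That the comparison of AEs between arms is biased by a known amount.** The intervention arm has eight consultations and the control arm one call of up to 15 minutes, but contact time does not measure how many AEs are found or missed. How AE sources are combined in tables may properly be left to the analysis plan, which is not shown.

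**Conclusion.** The contradiction stands. A stated forwarding rule defeats two stated commitments in the same section for non-serious AEs told only to the physiotherapist. It should be corrected, but it is modest in weight. The number of events affected cannot be derived from the protocol, and the likely harm is small. The conclusion rests on the protocol text alone and would weaken if the AE procedure or the notes template already requires forwarding or extraction. The section number and the committee name are editorial errors that make the route harder to follow.

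**What to change.** 1. In section 11, replace the seriousness condition with a rule that the physiotherapist forwards every AE to the research team: serious ones immediately, others before the next fortnightly section 1.4 meeting. The recipient should not administer or enter participant-reported data, because section 5.5 keeps those who do so blinded.
2. Extract AEs from notes already returned into the AE log before unblinding.
3. In the AE row of section 4.6, add the consultation notes as a source and change the reference from section 7 to section 11.
4. Name the receiving committee consistently with section 1.4, which already reviews reported AEs.
5. Report all logged AEs from every source, labelled by source. Alongside that full listing, and not instead of it, show questionnaire-reported AEs by arm as the like-for-like comparison. Questionnaires alone would leave no place for AEs reported directly to the team, or for events in women who withdraw before week 17. This item can sit in the analysis plan.

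The cost is a minor amendment, a short form when an event occurs, some extra low-grade items at an existing meeting, and a reading of the intervention-arm notes (36 sets at the planned size) that are already due for fidelity review. On the section 4.5 dates, the last 17-week follow-up was due by May 2024, before version 8 of 3 June 2024, but the protocol does not say whether that schedule was kept. If treatment has ended, item 1 helps no further participant in this trial, and the extraction and source corrections are what remain.

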## 12. STATISTICAL METHODS

### 12.1 Sample Size Estimation

We aim to detect a minimal clinically important difference (MCID) of 2.5 units [35] over 17 weeks in the primary outcome of change in urinary incontinence measured using the ICIQ-UI SF[34]. The sample size calculation accounts for potential clustering by physiotherapists in the intervention arm. Based on previous research[35], we assume a conservative between-participant standard deviation of 3.2 units. We have also assumed a conservative correlation between baseline and 17-week scores of 0.4, an intra-cluster correlation of 0.05 and 3 physiotherapists treating approximately 10 patients each. With these parameters, we need 30 women per arm to achieve 80% power to detect the MCID at a 0.05 significance level. Allowing for 15% attrition, we will recruit 36 women per arm (in total n=72).

### 12.2 Statistical Analysis Plan

All analyses will be described *a priori* in a detailed Statistical Analysis Plan and published while biostatisticians are blinded to treatment allocation. Demographic and baseline characteristics of participants will be summarised as appropriate (means and standard deviations for continuous variables that appear to be distributed approximately symmetrically, medians and interquartile ranges for other continuous variables, counts and percentages for categorical variables). Main comparative analyses between groups will be performed using intention-to-treat. Constrained longitudinal data analysis will be used to analyse continuous outcomes, including the primary outcome. The response will consist of all continuous outcomes (baseline, 17 weeks and 52 weeks) and the model will include factors representing treatment group, time (categorical), and a group-by-time interaction, with the restriction of a common baseline mean across treatment groups. Models will include the stratification

variable (radiotherapy) and random effects for physiotherapist (intervention arm only). The mean change in urinary incontinence (primary outcome) and other continuous outcomes (ICIQ-LUTSqol, PFBQ, EQ-5D-5L, UTAUT-II domains 1-9, METminutes (walking, moderate-intensity activities, vigorous-intensity activities) from baseline to each follow-up time-point between the two intervention groups will be obtained. The primary hypothesis will be evaluated by obtaining the estimated differences between the two intervention arms in mean change in urinary incontinence score from baseline to 17-weeks post-commencement of treatment (primary time point), two-sided 95% confidence intervals and p-values. These models provide valid inference in the presence of missing data if the data are missing at random. Standard diagnostic plots will be used to check model assumptions. Treatment effects at 52 weeks post-randomisation (secondary time point) will be estimated to assess maintenance of treatment effects for all outcomes except UTAUT-II domains 1-9 for which only 17-week follow-up data will be collected.

The binary secondary outcomes (PGIC and physical activity category) will be compared between groups separately using logistic regression, adjusting for the stratifying variable of radiotherapy, and fit using generalized estimating equations to account for clustering, with results reported as risk ratios and risk differences. Poisson regression models fitted using generalized estimating equations will be used for secondary count outcomes (number of leakage episodes overall and by severity and provocation, number of continence pads used).

The economic evaluation will have a societal perspective and will assess both the cost of the intervention at 17 weeks and the cost-effectiveness and cost-utility of the intervention group *versus* the control group at 52-weeks. Quality-adjusted life years (QALYs) gained [56] for the intervention compared to control at 52 weeks will be assessed. QALYs will be calculated based on utility scores using the EQ-5D-5L [44, 45] at baseline and 52 weeks. QALYs will also be calculated using the ICIQ-LUTSqol [42], a condition specific quality of life measure, at baseline and 52 weeks. Analysis will be combined with the primary clinical outcome measure to establish the incremental cost-effectiveness ratio of the intervention. The difference in participant resource use related to incontinence (e.g. pad use, medication use, health service use) and productivity lost between baseline and 52 weeks will be compared for intervention and control groups. The association between utility gains on the EQ-5D-5L and productivity will be compared between the intervention and control groups. The 52-week economic evaluation will be reported separate from the main trial.

